## Abstract

**Introduction:**

Necrotising enterocolitis (NEC) is a potentially devastating neonatal disease. A temporal association between red cell transfusion and NEC is well described. Observational data suggest that withholding enteral feeds around red cell transfusions may reduce the risk of NEC but this has not been tested in randomised trials; current UK practice varies. Prevention of NEC is a research priority but no appropriately powered trials have addressed this question. The use of a simplified opt-out consent model and embedding trial processes within existing electronic patient record (EPR) systems provide opportunities to increase trial efficiency and recruitment.

**Methods and analysis:**

We will undertake a randomised, controlled, multicentre, unblinded, pilot trial comparing two care pathways: continuing milk feeds (before, during and after red cell transfusions) and withholding milk feeds (for 4 hours before, during and for 4 hours after red cell transfusions), with infants randomly assigned with equal probability. We will use opt-out consent. A nested qualitative study will explore parent and health professional views. Infants will be eligible if born at <30+0 gestational weeks+days. Primary feasibility outcomes will be rate of recruitment, opt-out, retention, compliance, data completeness and data accuracy; clinical outcomes will include mortality and NEC. The trial will recruit in two neonatal networks in England for 9 months. Data collection will continue until all infants have reached 40+0 corrected gestational weeks or neonatal discharge. Participant identification and recruitment, randomisation and all trial data collection will be embedded within existing neonatal EPR systems (BadgerNet and BadgerEPR); outcome data will be extracted from routinely recorded data held in the National Neonatal Research Database.

**Ethics and dissemination:**

This study holds Research Ethics Committee approval to use an opt-out approach to consent. Results will inform future EPR-embedded and data-enabled trials and will be disseminated through conferences, publications and parent-centred information.

**Trial registration number:**

ISRCTN registry ISRCTN62501859; Pre-results.

Strengths and limitations of this studyNecrotising enterocolitis (NEC) is a rare but potentially devastating neonatal disease, occurring predominantly in the most preterm infants. Neonatal trials to-date have not been adequately powered to detect realistic reductions in NEC.In this prospective, randomised pilot trial we will evaluate the feasibility of a data-enabled neonatal trial with processes embedded within an existing electronic patient record (EPR) system; accuracy and completeness of trial data will be validated at source.In this individually randomised, comparative effectiveness trial we will pilot opt-out consent and explore parent and health professional views of this approach in a nested qualitative study.We will evaluate the feasibility of EPR-embedded randomised comparative-effectiveness trials using a simplified opt-out consent for efficient, quicker and less resource burdensome neonatal trials at scale.

## Background

Necrotising enterocolitis (NEC) is among the most potentially devastating neonatal diseases and has a mortality of up to 33%, the most severe form (requiring surgery or resulting in death) affects about 5% of infants born at <30 gestational weeks^1^; survivors are at high risk of long-term health^2^ and developmental problems.^3 4^ Prevention of NEC has been identified as one of the most important research uncertainties in the field of preterm birth.^5^ The pathogenesis of NEC is incompletely understood, however a temporal association between red cell transfusion and the subsequent development of the disease is well described.^6 7^ This ‘transfusion associated NEC’ may be more severe^8^ with higher mortality.^9 10^ The mechanism thought to underpin this relationship links milk feeds and packed red cell transfusion to NEC through altered mesenteric blood flow and intestinal barrier function; this is supported by animal^11^
^12^ and human studies^13^
^14^
^15^. Understanding the link between NEC and blood transfusion is of particular importance given that almost all very preterm babies will have a red cell transfusion and many will receive multiple transfusions^16^.

Stopping milk feeds around the time of packed red cell transfusion is currently practised in some neonatal settings to reduce the risk of NEC, putatively by maintaining more physiological intestinal blood flow.^17^ This practice has not, however, been tested in an adequately powered randomised trial, and there are physiological reasons why stopping milk feeds in preterm infants may lead to harm. Interrupting enteral feeding prolongs the time taken to reach full milk feeds, which is associated with invasive infection^18^, and may paradoxically be associated with an increased risk of NEC 19. One small, single-centre randomised pilot trial has assessed withholding enteral feeds around red cell transfusion but was underpowered to detect a difference in NEC.^20^ A systematic review of observational studies^21^ identified seven historical control studies including 7492 preterm infants; these studies were at high risk of bias including regression to the mean and ascertainment bias. Pooled results found an association between withholding feeds in the peritransfusion period and a reduced risk of NEC. The authors concluded that adequately powered randomised controlled trials are needed to confirm these findings.

There is considerable variation in current UK practice in relation to withholding enteral feeds during packed red cell transfusion in preterm infants: a 2011 survey of UK neonatal units (68% response rate) demonstrated that 35% of UK units routinely withheld enteral feeds during packed red cell transfusion.^22^

If withholding enteral feeds around the time of packed red cell transfusion reduces the risk of NEC, then implementing this simple practice will reduce the mortality and long-term complications of NEC. Conversely, if the safety of continued feeding can be demonstrated, this will facilitate increased and consistent feeding with breastmilk, which has well described short-term and long-term benefits.

NEC is rare and occurs at a higher incidence in the most preterm infants and so trials targeting NEC need a large number of very preterm infants, who are themselves rare. As a result, no previous trial has been powered to look at NEC and there is no intervention to prevent NEC supported by high-quality randomised evidence. Methologies that have been proposed to improve efficiency and recruitment into randomised trials include the use of simplified opt-out approaches to consent,^23^ and embedding trial processes into existing electronic patient record (EPR) systems.^24^

The objectives of this pilot trial are:

To determine whether a large multicentre trial addressing the following question is feasible: *among preterm infants (patient), does the practice of withholding enteral feeds around the time of blood transfusion (intervention), compared with continued enteral feeding around the time of blood transfusion (comparator), lead to a reduction in severe necrotising enterocolitis (outcome)?*
To determine whether clinical trial processes (identifying participants, randomisation and data collection) can be successfully integrated into existing neonatal EPR systems, and whether trial data can be extracted from routinely recorded clinical data held in the National Neonatal Research Database (NNRD).To determine whether using a simplified opt-out consent process is feasible and acceptable to parents and health professionals.

## Methods

### Design

The WHEAT trial is a randomised controlled, unblinded, multicentre, pilot trial comparing two care pathways. The primary metrics of feasibility are recruitment, data completeness and data accuracy; clinical outcomes include mortality and NEC. Infants will be randomised with a 1:1 allocation ratio (using permuted blocks of variable size), stratified within neonatal unit by gestational age at birth and infant sex. Trial processes will be embedded within neonatal EPR systems and all outcome data will be extracted from data that are routinely recorded within the existing neonatal EPR systems (BadgerNet and BadgerEPR), and held in the NNRD.

The trial will recruit infants from neonatal units within two neonatal networks in England: Northwest London Neonatal Network and Southern West Midlands Neonatal Operational Delivery Network. Recruitment will be for 9 months (15 October 2018 to 30 June 2019), with data collection continuing for a further 3 months, until all trial infants have finished follow-up at 40+0 corrected gestational weeks or neonatal discharge if sooner.

### Eligibility criteria

Inclusion criteria:

Preterm birth at <30+0 gestational weeks+days.

Exclusion criteria:

Parent(s) opted out of trial participation.Packed red cell transfusion with concurrent enteral feeds prior to enrolment. (Infants who have received a packed red cell transfusion while nil-by-mouth are eligible; buccal colostrum will not be counted as enteral feeding.)Infants where enteral feeding is contraindicated in the first 7 days after birth (eg, congenital abnormality).

### Interventions

Both comparator pathways of care are standard in the UK; the WHEAT trial is a pilot comparative effectiveness trial. The two care pathways that will be compared are:

Withholding feeds around transfusion: all enteral feeds will be discontinued (the infant will be placed nil by mouth) for a period of 4 hours prior to packed red cell transfusion, during the packed red cell transfusion and until 4 hours post packed red cell transfusion. During this period (~12 hours), hydration and blood glucose will be maintained according to local practice, commonly by provision of parenteral nutrition or intravenous dextrose. Four hours after the red cell transfusion has finished, feeds will be restarted in the manner in which they were being received prior to the decision to transfuse. This duration of withholding feeds will follow the approach used in other trials^20^ and observational studies,^21^ and identified to be the most acceptable in a survey of UK neonatal units.Continuing feeds around transfusion: enteral feeds will continue to be given prior, during and after the packed red cell transfusion, in the manner in which they were being given prior to the decision to transfuse.

Infants will remain allocated to the same care pathway until 34+6 weeks+days gestational age.

In order to ensure that this pragmatic trial is as generalisable as possible to current practice, blood transfusions will be administered when clinically indicated according to local packed red cell transfusion guidelines. Data will be collected about pretransfusion haemoglobin level for trial participants. Other concomitant care, including speed of increase of enteral feeds and choice of milk, for both the withholding feeds around transfusion pathway and the continuing feeds around transfusion pathway of care will be according to locally defined practice.

### Outcomes

Feasibility outcomes:

Recruitment: proportion of infants <30 weeks of gestation admitted whose parents agree to trial involvement and the infant is randomised in the WHEAT trial.Retention: proportion of of recruited infants where outcome data are available up to the end of the follow-up period.Compliance: proportion of recruited infants who correctly received their allocated care pathway around all packed red cell transfusions between randomisation and 34+6 gestational weeks+days.Data completeness: proportion of missing data for each data item reported as a baseline characteristic or an outcome.Data accuracy: proportion of cases where the following data items are correctly recorded when compared with source data (clinical notes or EPR data).Severe NEC: all infants who had a diagnosis of non-severe NEC and a random sample of 25% of infants who did not have a diagnosis of NEC will have their source data verified to ensure that they do not meet the criteria for severe NEC; 25% was selected for pragmatic reasons.Spontaneous intestinal perforation.All-cause mortality.Central line associated blood stream infection.

Clinical outcomes:

All clinical outcomes will be assessed from randomisation to 40+0 weeks of gestation or neonatal unit discharge, whichever occurs first.

Severe NEC: histologically or surgically confirmed, or recorded in part 1 the death certificate. These infants will be identified as described in Battersby *et al*,^25^ which will include infants recorded as being transferred for surgerySpontaneous intestinal perforation: histologically or surgically confirmed, or recorded in part 1 the death certificate.All-cause mortality.Total duration of neonatal care in days: including all levels of care (intensive care, high dependency care, special care and ordinary care).Duration of any parenteral nutrition in days.Number of days with a central venous line in situ.Number of central line associated blood stream infections defined according to National Neonatal Audit Programme 2017 definition^26^
Growth: change in birth weight and head circumference for gestational age SD score.

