### Ethics and dissemination

Because both the care pathways that are being compared are part of standard UK practice, WHEAT is using a simplified model of consent. This means that parents will have the WHEAT trial explained to them and will be asked to ‘opt out’ if they do not want their infant to be randomised and enrolled in the trial. Parents will be approached shortly after their infant is admitted to the neonatal unit (in most cases within the first 24 hours). There is no upper time limit as to when trial discussions can take place. Parents will be able to opt out of the WHEAT trial at any point. Neonatal health professionals will be prompted within the EPR to explain WHEAT to parents of eligible infants and to provide them with an information leaflet. If parents opt out this will be recorded in the EPR. If parents do not opt out and are happy for their infant to take part in WHEAT, randomisation will occur through the EPR. Enrolment of the infant and the allocation will be notified to the local team through the EPR. Because of the opt-out nature of WHEAT there will not be a signed consent form.

A qualitative exploration of the opt-out consent and recruitment process, and trial procedures will be conducted following the end of recruitment. Qualitative interviews will be undertaken with both parents that consented to the trial and health professionals from the recruiting sites.

Due to the common nature of packed red cell transfusion in the trial population (infants born at <30+0 gestational weeks+days), health professionals will explain the WHEAT trial and opt-out process shortly after birth (in most cases within the first 24 hours). A minority of infants will not receive a packed red cell transfusion during their neonatal unit stay. These will not be included in the main analysis population of clinical outcomes.

Results will be presented at national and international academic conferences and published in peer-reviewed scientific publications. Protocol author HR will work with the neonatal charity Bliss to produce parent-centred information for dissemination through social media, online and to be distributed on neonatal units.

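### Compliance is calculated over all recruited infants, including those with no transfusion while enterally fed in the compliance window, who had no pathway to comply with

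*Protocol article*

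**What the plan says.** The Outcomes section of the protocol article defines compliance as the "proportion of recruited infants who correctly received their allocated care pathway around all packed red cell transfusions", counted from randomisation to 34+6 weeks. Statistical methods adds a 95% CI for feasibility outcomes and reporting of compliance by arm and for both arms combined. It does not narrow the denominator. The list of changes to the statistical analysis revises the recruitment denominator and the data completeness measure, and leaves compliance as it stands.

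Ethics and dissemination explains that families are mostly approached within a day of birth, so most infants would be enrolled before the need for transfusion is known. It then says "A minority of infants will not receive a packed red cell transfusion during their neonatal unit stay", followed by "These will not be included in the main analysis population of clinical outcomes". That exclusion covers clinical outcomes only. Background says "almost all very preterm babies will have a red cell transfusion", without a figure.

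Under Interventions, the withholding pathway stops enteral feeds around the transfusion. The continuing pathway leaves feeding as it was before the transfusion was decided on. Eligibility criteria adds "Infants who have received a packed red cell transfusion while nil-by-mouth are eligible".

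**The concern.** A compliance figure should show whether staff followed the allocated pathway when the allocation called for something. Infants with no transfusion between randomisation and 34+6 weeks gave no such occasion. Nor did infants transfused in that window only while receiving no enteral feeds: the withholding pathway is already met, and the continuing pathway leaves an unfed infant unfed. With both groups in the denominator, the figure mixes adherence with lack of exposure.

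The article also removes never-transfused infants from the clinical-outcome population but not from compliance. The two results therefore describe different sets of infants. Compliance from the pilot is a natural input when judging how well the pathways could be kept apart in the planned main trial, and a figure diluted by unexposed infants would mislead there.

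**Working it through.** **No figure to reproduce.** The article gives no expected compliance, no compliance threshold and no transfused share. What follows shows how the written rule behaves under assumed inputs.

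**Inputs**
- N = 250, the upper end of the recruitment estimate (Sample size).
- u, the share of recruited infants with no transfusion while enterally fed between randomisation and 34+6 weeks. Not given; assumed 10% to 50%. It covers infants never transfused, and those transfused only before randomisation, only after 34+6 weeks, or only while unfed.
- c, compliance among the remaining (exposed) infants. Not given; assumed 60% to 90%.

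**Formulas**
- Unexposed infants scored compliant: reported = u + (1-u)c. The shift from c is u + (1-u)c - c = u(1-c), upward.
- Unexposed infants scored as not having received the pathway: reported = (1-u)c. The shift is uc, downward.
- Denominator restricted to exposed infants: reported = c, on N(1-u) infants.

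**Results** (95% CIs are Wilson intervals)

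| u | c | Scored compliant | Scored not compliant | Restricted denominator |
|---|---|---|---|---|
| 10% | 90% | 0.10 + 0.90×0.90 = 91% | 0.90×0.90 = 81% | 90% on 225 (85.4-93.3%) |
| 20% | 70% | 0.20 + 0.80×0.70 = 76% | 0.80×0.70 = 56% | 70% on 200 (63.3-75.9%) |
| 30% | 70% | 0.30 + 0.70×0.70 = 79% | 0.70×0.70 = 49% | 70% on 175 (62.8-76.3%) |
| 50% | 60% | 0.50 + 0.50×0.60 = 80% | 0.50×0.60 = 30% | 60% on 125 (51.2-68.2%) |

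The upward shifts are 0.10×0.10 = 1 point, 0.20×0.30 = 6 points, 0.30×0.30 = 9 points and 0.50×0.40 = 20 points. In the third row, the interval around 79% on all 250 infants is 73.5-83.6%, which excludes the 70% seen in exposed infants.

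**Which scoring applies.** The definition asks for correct care around all transfusions in the window. An infant with none meets that condition vacuously, so counting the infant as compliant is the natural reading. The wording also requires that the pathway was received, so scoring the infant as a failure cannot be ruled out. In the third row, the same data could be reported as 79% or 49%.

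**The case against.** **The full protocol or the SAP may settle the scoring.** How to count infants without a transfusion is often left to those documents, which are not shown. This stands for the scoring rule. It does not stand for the denominator, which the article fixes as recruited infants and which its list of changes does not touch.

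**The effect may be small.** This stands in part. Background says nearly all very preterm infants are transfused, and Ethics and dissemination calls the rest a minority. However, u also includes infants transfused only while unfed or only outside the window, and the article quantifies neither group. The sentence in Eligibility criteria about transfusion while nil-by-mouth concerns the time before enrolment. It shows that such transfusions occur, not how many infants have only those within the window.

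**Compliance may not be a primary metric.** The abstract says "Primary feasibility outcomes will be rate of recruitment, opt-out, retention, compliance, data completeness and data accuracy", but Design says "The primary metrics of feasibility are recruitment, data completeness and data accuracy". The abstract's list also retains opt-out, which the list of changes says will not be reported. So a reader might infer that a primary result is distorted, but the article supports that status in one place and not in the other.

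**Stronger inferences that the article does not support.**
- A reader might object that all-or-nothing scoring over every transfusion is an error, because it falls as the number of transfusions rises. It is a strict but legitimate per-infant measure, and the article states it plainly.
- A reader might infer a bias between arms from differing transfusion practice. Transfusion follows local guidelines in both arms and randomisation is stratified by unit, so nothing in the article points to such a difference.
- A reader might infer that the error has a known direction. Inflation follows from the natural reading, but the other scoring gives deflation.

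**Conclusion.** The point holds as a fault in the stated denominator. All recruited infants are counted, including those who had nothing to comply with, and no section corrects this for compliance. On the natural reading the figure is too high by u(1-c), anywhere from 1 point (u = 10%, c = 90%) to 20 points (u = 50%, c = 60%) over the assumed ranges. On the other reading it is too low by uc. Both inputs are assumptions, and the article's qualitative remarks suggest that the never-transfused part of u may be small.

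This is a recommended correction, not a must-fix. The article ties no progression decision to compliance, Design does not list it among the primary metrics, and the pilot makes no comparison between arms.

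**What to change.** Define the compliance denominator as recruited infants with at least one packed red cell transfusion between randomisation and 34+6 weeks, given while they were receiving enteral feeds when the transfusion was decided on. If feeding status at that point cannot be obtained reliably, the minimum is infants with at least one transfusion in the window. Report the number of recruited infants with no qualifying transfusion, by arm and combined, beside the compliance figure.

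A per-transfusion rate, with a CI that allows for clustering within infant, is an optional supplement and not a correction. Feeding status at later transfusions could be affected by the earlier allocation, so that rate would need cautious reading.

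The cost is a change of outcome wording and one extra reported count. Judging whether feeds were withheld or continued already requires knowing how the infant was being fed beforehand, although the article does not say whether routine records capture this for every transfusion. The interval widens a little: at c = 70% and u = 20% it is 63.3-75.9% on 200 infants (12.6 points wide), against 70.3-80.9% (10.6 points) around the 76% that the written denominator would give on 250.

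### Compliance is measured over all recruited infants, including those with no transfusion in the window, in whom the allocated pathway was never applied

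*Protocol article*

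**What the plan says.** Under Outcomes, compliance is a feasibility outcome defined as the "proportion of recruited infants who correctly received their allocated care pathway around all packed red cell transfusions", counted from randomisation to 34+6 weeks. The denominator is every recruited infant. Statistical methods adds that compliance is reported for each arm and for both arms combined, with 95% confidence intervals for the feasibility outcomes. It mentions no figure limited to transfused infants.

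Under Ethics and dissemination, the article says that "A minority of infants will not receive a packed red cell transfusion during their neonatal unit stay", and continues: "These will not be included in the main analysis population of clinical outcomes". That exclusion covers clinical outcomes only. The list of changes to the statistical analysis alters the recruitment denominator and the completeness definition but does not mention compliance.

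Three other statements bear on the point:

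- Background says that "almost all very preterm babies will have a red cell transfusion and many will receive multiple transfusions".
- Eligibility criteria, on transfusions before enrolment, says that "Infants who have received a packed red cell transfusion while nil-by-mouth are eligible".
- Interventions describes the withholding pathway as one in which "the infant will be placed nil by mouth" from 4 hours before until 4 hours after transfusion. In the continuing pathway, feeds are given "in the manner in which they were being given prior to the decision to transfuse".

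**The concern.** Compliance is meant to show whether staff will follow the allocation when a transfusion takes place. An infant with no transfusion between randomisation and 34+6 gives no information on that. Such infants arise by design, because the trial is explained in most cases within 24 hours of birth, before the need for transfusion is known. They include infants never transfused, infants transfused only before randomisation, and infants transfused only after 34+6.

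The authors recognised these infants when setting the population for clinical outcomes, yet the compliance definition keeps them. The definition also does not say how they are scored, so the same data can give two different figures. A pilot that informs a main trial needs compliance, overall and by arm, from infants in whom the pathway could be followed or breached.

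**Working it through.** **Stated figures.** The article gives no expected compliance and no compliance threshold, so there is no figure to reproduce.

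**Inputs.**

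- Denominator: all recruited infants (Outcomes).
- Recruitment: up to 250 (Sample size).
- v, the share of recruited infants with no transfusion from randomisation to 34+6: not given. Assumed 5–10%, in line with the Background remark that almost all are transfused.
- c, compliance among infants with at least one transfusion in the window: not given. Assumed 60–90%.

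**Formulas.**

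- Denominator limited to transfused infants: c.
- All recruited, untransfused infants counted as compliant: v + (1−v)c, which exceeds c by v(1−c).
- All recruited, untransfused infants counted as not compliant: (1−v)c, which is below c by vc.
- The gap between the two scorings is v + (1−v)c − (1−v)c = v, whatever the value of c.

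**Results.**

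| v | c | Counted compliant | Change (points) | Counted not compliant | Change (points) |
|---|---|---|---|---|---|
| 5% | 60% | 62.0% | +2.0 | 57.0% | −3.0 |
| 5% | 80% | 81.0% | +1.0 | 76.0% | −4.0 |
| 5% | 90% | 90.5% | +0.5 | 85.5% | −4.5 |
| 10% | 60% | 64.0% | +4.0 | 54.0% | −6.0 |
| 10% | 80% | 82.0% | +2.0 | 72.0% | −8.0 |
| 10% | 90% | 91.0% | +1.0 | 81.0% | −9.0 |

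**In counts.** Take 250 recruited, v = 10% and c = 80%. Then 25 infants have no transfusion in the window, 225 do, and 180 of those comply.

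- Transfused infants only: 180/225 = 80% (Wilson 95% CI 74.3–84.7%).
- Literal reading of the definition: (180 + 25)/250 = 82% (76.8–86.3%).
- Opposite scoring: 180/250 = 72%.

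**By arm.** If v is the same in both arms, either scoring shrinks the difference in compliance between arms by the factor 1−v. With v = 10% and true compliance of 90% and 60%, the literal reading gives 91% and 64%. A gap of 30 points is shown as 27.

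**Infants transfused only while nil by mouth.** Under the Interventions wording, an infant with no feeds from 4 hours before to 4 hours after the transfusion satisfies both pathways: there is nothing to withhold, and feeding continues as before at nil. This holds only if the infant stays nil by mouth for the whole period. If feeds begin during the transfusion or in the 4 hours after it, the withholding pathway is breached. The article does not say how many infants fall in this group.

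**The case against.** The strongest reply is that the article never says untransfused infants count as compliant. The definition asks that an infant correctly received the pathway, and an infant with no transfusion arguably received nothing. On that view the bias is downward, and the scoring rule may stand in the full protocol or the analysis plan. This is fair as to direction: upward bias is the literal reading of the word *all*, not a stated rule. It does not rescue the denominator, which the article itself fixes as recruited infants and which distorts the figure under either scoring.

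The reply on size also stands. The effect under the literal reading is small in the assumed range, the confidence intervals overlap widely, and there is no threshold for a shift of this size to cross.

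A reader might infer several stronger claims that the documents do not support:

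- *That compliance will be heavily inflated.* Shares of 20–40% would be needed for large effects. The article gives no basis for them, and its Background statement points the other way for infants never transfused.
- *That any infant transfused while nil by mouth could not deviate.* This fails if feeds start before the 4 hours after transfusion have passed. The eligibility sentence concerns transfusions before enrolment, so it says nothing about how often this happens in the compliance window.
- *That comparisons between gestational strata or units are distorted.* No such comparison of compliance is planned.
- *That the primary denominator should be limited to infants fed at transfusion, or whose feeds were stopped only for it.* In an unblinded trial this needs a judgement on why feeds were stopped. It could remove real non-compliance in the continuing arm from view.

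**Conclusion.** The point holds as a fault in a stated definition. The compliance denominator includes infants in whom the pathway was never applied, and the article leaves their scoring open. Under the literal reading the excess is v(1−c), or 0.5 to 4 points for v of 5–10% and c of 60–90%. Under the opposite scoring the shortfall is vc, or 3 to 9 points over the same ranges. The choice of scoring alone moves the figure by v.

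These sizes rest on assumed values of v and c. The Background statement concerns any transfusion, so it supports a small never-transfused share but does not fix the share with no transfusion in the window. The extra effect of infants transfused only while nil by mouth throughout the pathway period cannot be sized from the article. The correction is worth making because compliance is a feasibility outcome and the change is cheap, not because a large error has been shown.

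**What to change.** Define compliance as the proportion of randomised infants with at least one packed red cell transfusion between randomisation and 34+6 who correctly received the allocated pathway around all such transfusions.

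Report by arm, on separate lines:

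- the number with no transfusion in the window;
- the number transfused only while nil by mouth throughout the pathway period.

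Add a sensitivity figure that leaves out the second group.

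The cost is a revised sentence in the outcome definition, the extra table lines and one further calculation. Identifying the second group needs feeding status across the whole pathway period, but no judgement on why feeds were stopped. The denominator becomes smaller, the interval somewhat wider, and the figure possibly slightly less favourable. No clinical rule changes.
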